### Planned analyses

Intention-to-treat and per-protocol statistical analyses will be conducted by the investigators, in close collaboration with a statistician experienced in analysis of hypoglycaemia data. Before the randomisation code will be added to the cleaned dataset, a thorough plan for statistical analyses will be elaborated and accepted by the statistician and investigators. The cross–over design makes it possible to accommodate the individual patient’s event parameters and continuous parameters. The per-protocol analyses will include only patients who have completed the first treatment period and at least 6 months of the second treatment period (cross-over plus three months maintenance).

Endpoints will be compared between treatment groups as an analysis of differences in rates during the last nine months of each treatment arm. In the simplest model this difference is assumed to be normally distributed and tested as such under the assumption that the HbA_1c_ levels are comparable during the two treatment arms. If necessary a more specific analysis in a negative binomial distribution model and/or a Poisson model will be used to describe the number of events through a suitable link function as a linear function of individual patient levels, treatment effects, treatment period, and mean HbA_1c_ level during endpoint assessment. Individual differences in the observation period will be adjusted for in the analyses.

For continuous parameters a co-variance analysis will be conducted.

The level of statistical significance is chosen as *p* < 0.05 (two-sided).

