## Methods/design

### Design, comparative treatment regimens and study duration

A Danish investigator-initiated, cross-over, multi-centre study conducted in a prospective, randomised, open, blinded endpoint (PROBE) design (Fig. 1). Patients are randomised to treatment with basal-bolus therapy with insulin degludec and insulin aspart (Tresiba®/NovoRapid®) or insulin glargine U100 and insulin aspart (Lantus®/NovoRapid®) in random order. Each treatment period lasts for 12 months. The first three months of each treatment period is a run-in or cross-over phase to be used for insulin dose adjustment and stabilisation of treatment regimens. Endpoints are assessed during the last nine months of each treatment arm (Fig. 1). Optional admissions for overnight plasma glucose measurements and six days of ambulatory blinded continuous glucose monitoring will be performed after 6 and 12 months in each treatment arm (Fig. 1).

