**Fig. 1 Fig1:**
[figure not shown]
Study design.  Endpoint assessment periods.  Admission for overnight plasma glucose monitoring and/or 6 days of ambulatory 24 h continuous glucose monitoring

Insulin doses will be adjusted according to the individual patient’s need at the discretion of the individual physician. Patients are instructed to perform and record 4-point self-monitored blood glucose (SMBG) profiles twice per week (before breakfast, before lunch, before dinner and at bedtime). A treat-to-target design is deliberately not used in order not to intervene with present glycaemic control and everyday clinical practice, which in itself may interfere with the risk of hypoglycaemia. We expect the individual patient to present the best obtainable glycaemic control with respect to risk of hypoglycaemia at inclusion, and we therefore strive for maintenance of baseline glycaemic control in both treatment periods. If, however, the glycaemic control is not acceptable we will strive for the best obtainable glycaemic control in both treatment periods, taking the risk of hypoglycaemia into account.

The HypoAna trial [5] showed significantly increased rates of severe hypoglycaemia during run-in and cross-over periods. Therefore, insulin doses are reduced at entrance into both treatment arms. A 20% reduction in both basal and bolus insulin dose is recommended when the patient changes from one insulin regimen to another, irrespective of the product. Rapid up titration by mandatory phone consultations weekly at week 1, 2 and 4 is followed by ad hoc titration at the investigators’ discretion.

The study is a once daily (QD) comparison between the insulins with long duration of action, i.e. degludec and glargine. Insulin degludec and insulin glargine U100 are administered subcutaneously in the thigh or in the abdominal wall with the evening meal. Correct injection technique is assured by a diabetes specialist nurse. The site of injection should be changed within the same anatomical region to avoid lipohypertrophy making insulin absorption more unpredictable.

The study was approved by The Regional Committee on Biomedical Research Ethics.

(#H-3-2014-101), the Danish Medicines Agency (#2014071615) and the Danish Data Protection Agency (I-suite no: 02945; #NOH-2014-018). The study is registered at www.eudract.ema.europe.eu (#2014–001942-24) and at www.clinicaltrials.gov (# NCT02192450). The Study is conducted in accordance with the Helsinki Declaration.

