## Statistics

### Power considerations

Rates and distribution of hypoglycaemic events are much skewed and unpredictable [6, 28]. The occurrence of hypoglycaemia is influenced by many factors, and by engaging in a study rates of hypoglycaemia usually are affected considerably.

Formal power calculations are therefore, not found feasible.

According to the power calculation and results from the HypoAna trial with a significant relative difference between treatment regimens of 30–40% concerning both primary and secondary nocturnal endpoints [5, 6, 8], we decided to include and randomise approximately 175 type 1 diabetes patients prone to severe hypoglycaemia (i.e. one or more episodes of nocturnal severe hypoglycaemia during the preceding two years).

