### Additional statistics

The obtained glycaemic control during the two treatment regimens will be evaluated through comparisons of HbA_1c_ levels after 12 months’ treatment including factors corresponding to treatment, treatment period and the individual patient level. Furthermore, SMBG profiles will be evaluated in addition to quantification of glucose variability during night-time and 6 days of CGM.

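### The simple endpoint analysis of this two-period cross-over names no period term, and adjustment for period depends on a fallback model with no stated trigger

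*Protocol article*

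**What the plan says.** Three statements in the protocol article bear on this.

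- **Planned analyses, simple model.** Endpoints are compared as differences in rates over the last nine months of each arm: "In the simplest model this difference is assumed to be normally distributed and tested as such". The only further assumption stated is that HbA1c is comparable in the two arms.
- **Planned analyses, count model.** "If necessary a more specific analysis in a negative binomial distribution model and/or a Poisson model will be used". It describes the number of events "as a linear function of individual patient levels, treatment effects, treatment period" and mean HbA1c. No criterion is given for when it becomes necessary.
- **Additional statistics, HbA1c.** The comparison after 12 months is made "including factors corresponding to treatment, treatment period and the individual patient level", with no condition attached.

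Planned analyses also says that individual differences in the observation period will be adjusted for. That concerns how long each patient was observed. It does not concern whether the observation fell in the first or the second treatment year.

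**The concern.** A test of the mean within-patient difference is a valid treatment comparison in a two-period cross-over if rates are the same in both periods or the sequences are equal in size, and it is fully efficient only in the first case. If rates drift between periods, patients who take degludec first and patients who take glargine first carry that drift with opposite signs. The spread of the differences grows, and with unequal sequences part of the drift is read as treatment effect. The article names the needed term for the count model and for HbA1c. As worded, the simple comparison of the hypoglycaemia endpoints is the one place where it is absent.

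**Working it through.** **Inputs from the article:** about 175 patients; 1:1 allocation in blocks of four within site; ten sites; two-sided 5% level; a 30–40% relative difference taken from an earlier trial. **Not given:** power, event rate, SD of the within-patient difference, period effect, drop-out rate. These are assumed below.

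**1. The article's own figure.** The 175 cannot be reproduced, because the article says formal power calculations were not feasible. As a bridge, use the paired normal formula N = ((z₀.₉₇₅ + z_power) × SD/δ)². At N = 175, δ/SD = 2.802/√175 = 0.212 for 80% power, or 0.245 for 90%. A 30–40% reduction then implies an SD of 1.22 to 1.89 times the control mean.

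**2. Algebra.** Let d be the degludec minus glargine rate, τ the treatment effect, and π the period 2 minus period 1 change. The mean of d is τ − π with degludec first and τ + π with glargine first. Let n1 be the number with glargine first, n2 the number with degludec first, and N = n1 + n2.

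- Bias without a period term: π(n1 − n2)/N.
- Added variance of d: π² × 4n1n2/N², which is π² when balanced.
- With a period term, the estimate is the average of the two sequence means of d. π cancels, assuming no carry-over.

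**3. Balanced sequences.** Shifts are fractions of the control mean. Example: SD 1.42, shift 0.30. The SE multiplier is √(1 + (0.30/1.42)²) = 1.022. Power is Φ(2.802 − 1.960 × 1.022) = 78.8%, against 80% with the term. Type I error is 2(1 − Φ(1.960 × 1.022)) = 4.5%.

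| Reduction; power with period term | SD / control mean | 30% shift: SE multiplier; power; type I error | 50% shift: SE multiplier; power; type I error |
|---|---|---|---|
| 30%; 80% | 1.42 | 1.022; 78.8%; 4.5% | 1.060; 76.5%; 3.8% |
| 30%; 90% | 1.22 | 1.030; 88.9%; 4.4% | 1.080; 87.0%; 3.4% |
| 40%; 80% | 1.89 | 1.013; 79.3%; 4.7% | 1.034; 78.1%; 4.3% |
| 40%; 90% | 1.63 | 1.017; 89.4%; 4.6% | 1.046; 88.3%; 4.0% |

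The loss is 0.6–1.2 points at 30% and 1.7–3.5 points at 50%.

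A simulation with skewed counts gives a similar picture. It assumed 75 patients per sequence, mean 4 or 12 events per nine months, gamma heterogeneity between patients (shape 1) and between periods within patient (shape 2 or 8), and a treatment ratio of 0.70, with 4,000 runs. With period-2 rates at 75% of period-1 rates, variance rises 3–9% and power falls by up to 1 point. At 50%, variance rises 13–33%. Power without and with the term is then 60.8 v 65.4%, 67.0 v 72.1%, 85.2 v 90.2% and 94.4 v 97.0%, a loss of about 3–5 points.

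**4. Unequal sequences.** With a 30% shift, the bias as a share of the control mean is:

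- 90:85: 5/175 × 0.30 = 0.9%, type I error 4.5–4.8%.
- 97:78: 19/175 × 0.30 = 3.3%, type I error 5.3–5.7%.
- 80:60: 20/140 × 0.30 = 4.3%, type I error 5.5–6.2%.

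Randomisation alone gives little imbalance. An incomplete block of four adds an imbalance variance of 0, 1, 4/3 or 1 per site. Ten sites give an SD of √(10 × (0 + 1 + 4/3 + 1)/4) = 2.9 patients and a maximum of 20 (11% of 175). Larger gaps would have to come from drop-out.

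A second simulation shows the bias at work. It assumed a glargine mean of 2 events, rate ratio 0.65, period-2 rates 40% lower, between-patient variance 1.5 and within-patient variance 0.6, with 6,000 runs. At 88:87, power without and with the term is 68.9 v 71.2%. With 97 degludec-first and 78 glargine-first patients it is 56.2 v 70.1%, and the estimated difference is −0.484 v −0.556. The formula agrees: the mean period effect is (0.80 + 0.52)/2 = 0.66, and 19/175 × 0.66 = 0.072. With the larger group on glargine first, the same shift would exaggerate the benefit of degludec.

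**The case against.** The strongest reply has three parts.

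**The detail is deferred.** The article promises a thorough analysis plan, agreed before the randomisation code is added to the cleaned data, and a journal article need not list every factor. It never excludes period, and comparing period differences between sequences could be read into its wording. This lowers the weight of the point. It does not remove it, because the article names a model, its assumption and a fallback, and it puts period in one model and not in the other.

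**The count model may be used anyway.** The article calls event rates much skewed, so the model that includes "individual patient levels, treatment effects, treatment period" may well be needed. That is fair, and it is why the simple model should not be called the fixed primary analysis. But with no criterion for the switch, adjustment for period is left open.

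**No drift between periods is documented.** A reader might infer that the protocol itself expects rates to differ between the two treatment periods, because "by engaging in a study rates of hypoglycaemia usually are affected considerably" (Power considerations). That sentence concerns joining a study and is given as a reason for not calculating power; it states no trend from one endpoint window to the other. The earlier trial "showed significantly increased rates of severe hypoglycaemia during run-in and cross-over periods" (Design, comparative treatment regimens and study duration), but here "Endpoints are assessed during the last nine months of each treatment arm", which leaves those phases out. This part of the objection stands in full.

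**Conclusion.** The point holds as a modest, conditional weakness. As worded, the simple endpoint comparison omits a term that the article uses elsewhere. If there is no period effect, omitting it does no harm. With near-balanced sequences, a 25–30% shift costs about 1 point of power or less (at most 1.2 in the cases above) and the test errs slightly on the conservative side. A shift of 50% costs roughly 2 to 5 points. Bias needs a period effect and unequal sequences together.

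Two further readings go too far. One is that power is lost whatever happens; the loss depends wholly on an assumed shift. The other is that the per-protocol completion rule would unbalance the sequences; it applies alike to both, and the article gives no reason to expect unequal loss. The larger effects, such as 56.2 v 70.1% power, combine a 40% fall in rates with an imbalance of 19 patients, close to the most that randomisation alone could produce. Event rates, spread, period shifts and drop-out are all assumptions here.

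**What to change.** State in the analysis plan that treatment period is a fixed term in whichever endpoint model is used.

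- **Simple normal model:** compare the within-patient period differences between the two sequences, which is equivalent to fitting patient, period and treatment.
- **Count model:** keep patient, treatment and period, with log observation time as offset.

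The cost is one line of text and one degree of freedom, with no new data. If there is no period effect, the result is essentially unchanged.

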### Additional statistics

The obtained glycaemic control during the two treatment regimens will be evaluated through comparisons of HbA_1c_ levels after 12 months’ treatment including factors corresponding to treatment, treatment period and the individual patient level. Furthermore, SMBG profiles will be evaluated in addition to quantification of glucose variability during night-time and 6 days of CGM.

## Laboratory analyses

HbA1c is measured at every visit (V1-V9). At V1 (randomisation), V5 (cross-over) and V9 (end of study) haemoglobin, haematocrit, plasma creatinine, plasma sodium, plasma potassium, total cholesterol, high and low-density lipoprotein cholesterols, triglycerides, and thyroid-stimulating hormone (TSH), T4 and T3 are measured.

Fasting C-peptide is only measured at randomisation (V1) and concentrations below 20 pmol/l (= 0.02 nmol/L) are considered C-peptide negative.

Urinary albumin excretion rate is determined in one overnight urine sample at V1 and repeated after one year at V5 and after 2 years at V9. This also applies to the biobank samples (serum, plasma, DNA and urine) which are gathered at V1, V5 and V9.

HbA1c is measured centrally at Nordsjællands Hospital Hillerød using High Performance Liquid Chromatography method on a Tosoh Automated Glycohemoglobin Analyzer.

All other analyses are performed locally by routine methods.

## Discussion

In contrast to almost all other studies in this field the HypoDeg trial includes only patients who are hypoglycaemia-prone. The HypoDeg trial will elucidate whether once-daily insulin degludec in comparison with once-daily insulin glargine U100 during basal-bolus therapy is advantageous in limiting the number of hypoglycaemic episodes in these patients who may have the greatest benefit from optimized basal insulin therapy.

This insulin trial is one of a few to systematically evaluate the risk of hypoglycaemia by simultaneous adjudication of events, reporting in diaries and observation by CGM [5–7].

The results may have a direct evidence-based impact on the patients and their health care professionals in choice of basal therapy.

## Data Availability

The datasets used and/or analysed during the current study are available from the corresponding author on reasonable request.

## Abbreviations

ADA: American Diabetes Association
CGM: Continuous glucose monitoring
CRF: Case Report File
CV: Coefficient of Variation
EASD: European Association for the Study of Diabetes
EQ-5D-3 L: EuroQol-5 dimension quality of life index
HbA1c: Haemoglobin A1c
HCS: Hypoglycaemia Confidence Scale
HFS: Hypoglycemia Fear Survey
ITSQ: Insulin Treatment Satisfaction Questionnaire
MDI: Major Depression Inventory
NPH: Neutral protamine Hagedorn
NYHA: New York Heart Association
PROBE: Prospective, randomised, open, blinded endpoint
QD: quaque die (one daily)
SCL-92: Symptom Checklist
SMBG: Self-monitored blood glucose
TSH: Thyroid-stimulating hormone
